Decompression with a nasogastric tube is carried out in order to calculate the average nasogastric tube output of each patient [total amount of drainage/duration]. For patients administered Gastrografin before surgery, only the output before the procedure is considered. Intravenous fluid therapy is performed.

Plain abdomen X-rays are done and maximal small intestine diameter is calculated. Duration of symptoms before admission and number of previous operations are also evaluated.

Subjects with ASIO who elect to undergo the surgical laparotomy are enrolled in the study; written informed consent is obtained from each individual and then they are randomized into the study groups. Laparotomic surgical procedure is carried out and existing abdominal cavity adhesions are documented. Subjects are submitted to adhesiolysis with bowel resection if necessary with or without anastomosis. The first group receive traditional treatment [control group] whereas the second group is treated with Icodextrin 4% before abdomen closure. The use of irrigants during surgery is not allowed. Peritoneal contamination is evaluated with cultures.

Per protocol the abdominal fascia is closed with a running PDS suture and the skin is closed with sutures or skin staples.

Only one abdominal drainage in allowed in case of bowel resection and it has to be removed 7 days after the operation.

In case of bowel leakage, the patient will no longer be included in the study results.

For all patients, perioperative parameters are recorded, including blood loss, total length of the midline incision, method of anastomosis, method and timing of incision openings and closures, corticosteroid use. Operative wounds are classified as clean, clean contaminated, and contaminated as described by Schwartz [9].

Morbility, mortality and postoperative stay are registered. A flow chart showing the protocol is illustrated in figure 1.

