**Figure 1 F1:**
[figure not shown]

The patients are followed-up for 5 years.

In case of reoperation for ASIO the procedure is carried out by a third party blinded to the patient's previous antiadhesive treatment: this surgeon evaluates incidence, location, severity, and extent of adhesions. The incidence of adhesions is assigned a severity score of 0 [no adhesions], 1 [filmy thickness, avascular], 2 [moderate thickness, limited vascularity], or 3 [dense thickness, vascularized].

Adverse events [AEs] are collected for the duration of the study, beginning at the time of randomization.

AEs are identified and described by the primary investigators.

In the control group, patients will be treated as in our daily surgical practice.

In the informed consent form, patients receive all the information about the study protocol, confidential data management and they fill up a questionnaire before signing or refuse.

There are not inconveniences caused to the patients. No incentives are planned for the patients regarding the operation or the follow-up.

There are not any additional risks for the treatment and control group: both groups have the standard surgical treatment and follow-up: icodextrin group is an antiadherences fluid with no adverse effects.

All the medical information obtained from the patients are kept confidential among the research scientists conducting the study.

The patients are free to withdraw from the study, whenever they want and without any obligation.

The study is approved by the ethical Committee of the S'Orsola-Malpighi Hospital, Bologna, Italy

The primary endpoints of our study are:

To evaluate the therapeutic role of Icodextrin 4% to reduce ASIO incidence

To reduce adherences rate [in case of reoperation for ASIO]

The onset of any other complications are recorded intraoperatively, postoperatively, at discharge, at 7-days, 1-month, 6-months, every year up to 5 years follow-up.

The primary outcomes are assessed every year [interim analysis] up to 5 years after the last enrolled patient.

The data generated by this study are analysed in two ways. The continuous numerical data are subjected to analysis of variance [ANOVA], this method being applicable to the discrimination of two continuous populations. Discrete data are analysed by the chi-squared test or Fisher exact test, as appropriate. Statistically significant differences between study treatments are based on p < 0.05.

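### Adhesions recorded at the index operation are not used when adhesions at reoperation are compared, which gives up some precision in a small subset

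*Protocol article*

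**What the plan says.** The relevant statements are all in the Methods of the protocol article.

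- **Index operation.** After consent and randomisation, "Laparotomic surgical procedure is carried out and existing abdominal cavity adhesions are documented". No grading scale is given for this record. Then "Subjects are submitted to adhesiolysis with bowel resection if necessary with or without anastomosis". The control group has usual treatment, "whereas the second group is treated with Icodextrin 4% before abdomen closure". In the order described, the index record comes before treatment.
- **Endpoint.** The second of the two primary endpoints is "To reduce adherences rate [in case of reoperation for ASIO" (text following Figure 1). At reoperation a blinded third party operates, and "this surgeon evaluates incidence, location, severity, and extent of adhesions". Severity is an absolute score: "The incidence of adhesions is assigned a severity score of 0 [no adhesions], 1 [filmy thickness, avascular", and so on up to 3. It is not a change from the index operation, and re-formed adhesions are not separated from new ones.
- **Analysis.** Two kinds of analysis are described: "The continuous numerical data are subjected to analysis of variance [ANOVA"; and "Discrete data are analysed by the chi-squared test or Fisher exact test, as appropriate". No covariate or stratification is named, and the index finding has no stated role.

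**The concern.** The adhesion comparison rests only on patients who are reoperated. That group is small, so chance differences between arms in index adhesions can be sizeable and precision is limited. A patient's index adhesions plausibly predict what is found later, through the individual tendency to form adhesions and through any adhesions left undivided. If so, an unadjusted test leaves that predictable variation in the error term.

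A second reason is that reoperated patients are selected after treatment. If worse index adhesions raise the risk of recurrence and icodextrin works, the fewer icodextrin patients who recur will tend to be those with worse index adhesions. Randomisation does not protect this subset comparison from such a difference. Adjustment for the index value can remove its measured part.

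At stake is the power, and to a small degree the fairness, of one of the two primary comparisons.

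**Working it through.** **1. The plan's own figure.** Inputs from Methods: recurrence 50% v 25%, 95% confidence (taken as two-sided 5%), 80% power. With mean proportion 0.375:

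n = [1.96 × √(2 × 0.375 × 0.625) + 0.842 × √(0.25 + 0.1875)]² / 0.25² = 57.7, so 58 per arm.

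The continuity correction, n/4 × [1 + √(1 + 4/(0.25n))]², gives 65.4, so 66. The stated 65 analysable per arm is reproduced to within one patient, and 88 enrolled implies a loss of 1 − 65/88 = 26.1%. This calculation concerns recurrence. It says nothing about the adhesion endpoint but supplies the numbers for the next step.

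**2. How many patients contribute.** 65 × 0.50 = 32.5 and 65 × 0.25 = 16.25, so about 33 v 16 if every recurrence is reoperated. If half are, about 16 v 8. If all 88 per arm were followed and every recurrence reoperated, 44 v 22.

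**3. Gain from adjustment.** Adjusting for a baseline with correlation rho multiplies residual variance by 1 − rho². The documents give neither rho nor an effect size for adhesions, so both are assumed. Power uses the noncentral t distribution, two-sided 5%, with noncentrality d/√(1 − rho²) × √(n₁n₂/(n₁ + n₂)) and one degree of freedom lost when adjusted.

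Example at 33 v 16, d = 0.5: √(528/49) = 3.283. Unadjusted noncentrality is 0.5 × 3.283 = 1.641 (47 df), power 36.3%. With rho 0.5 it is 0.5/√0.75 × 3.283 = 1.895 (46 df), power 45.9%.

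| Reoperated | Effect (SD) | Unadjusted | rho 0.3 | rho 0.5 | rho 0.6 |
|---|---|---|---|---|---|
| 33 v 16 | 0.50 | 36.3% | 39.2% | 45.9% | 51.9% |
| 33 v 16 | 0.65 | 55.2% | 59.1% | 67.4% | 74.3% |
| 33 v 16 | 0.80 | 73.0% | 76.9% | 84.3% | 89.5% |
| 16 v 8 | 0.50 | 19.7% | | 24.7% | |
| 16 v 8 | 0.65 | 30.0% | | 38.0% | |
| 16 v 8 | 0.80 | 42.4% | | 53.0% | |

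At 33 v 16 the gain is 3 to 4 points at rho 0.3, 10 to 12 at rho 0.5 and 16 to 19 at rho 0.6. At 16 v 8 it is 5 to 11 points at rho 0.5.

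**4. The 0-3 score itself.** Simulating latent normal values cut to 0-3 (33 v 16, latent rho 0.5, linear model on the score, 3000 trials) gives 50.6% to 58.6% at 0.65 SD and 67.3% to 74.4% at 0.8 SD. Type I error is 5.1% unadjusted and 5.6% adjusted.

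**5. Range restriction.** Steps 3 and 4 treat the reoperated patients as unselected. In fact all enrolled patients already have adhesive obstruction, and all assessed patients are reoperated for it, which shrinks the correlation. A simulation took 65 per arm, latent rho 0.5 and a latent effect of 0.674 SD (which gives 50% v 25%). Reoperation was driven by latent adhesions plus 0, 0.5 or 1 SD of noise, and the baseline was restricted as well. Power moved from 14.5% to 15.4%, 26.6% to 28.5% and 45.6% to 47.5%: gains of 1 to 2 points. With an unrestricted baseline the gain was 5 to 10 points.

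**6. Selection into reoperation.** If recurrence depends directly on index severity (probit slope 0.5 or 1.0 per SD, at 50% v 25%), reoperated icodextrin patients have index adhesions 0.21 or 0.33 SD worse than reoperated controls. The unadjusted estimate carries rho times that gap, at rho 0.5 about 0.105 or 0.165 SD against icodextrin. If reoperation is instead driven by the later adhesions themselves, as in step 5, adjustment helps little: against a true effect of 0.674 the unadjusted estimates were 0.20 to 0.46 and the adjusted 0.22 to 0.49. Another run with 0.5 or 1 SD of selection noise moved the estimate by about 0.06 SD.

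**The case against.** **Covariates belong in an analysis plan that is not shown.** In part this stands: the article does not rule out adjustment. But it does name the tests for its endpoints, and none uses the index finding, so the point rests on what is written.

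**Old adhesions contaminate the endpoint.** A reader might infer that the score at reoperation mixes pre-existing adhesions with those icodextrin should prevent. The document does not support this as the main problem. Adhesiolysis comes before icodextrin, so later adhesions are largely re-formed or new, and both are targets of treatment. Only undivided adhesions would be old, and the document does not say how complete adhesiolysis is.

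**The tests are valid without the baseline.** This stands. Leaving out a covariate does not by itself bias a randomised comparison. The bias here comes from restricting the endpoint to reoperated patients, and step 6 shows that adjustment may recover only a little of it.

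**The gain may be close to nothing.** This stands as a lower bound, given range restriction and an unknown rho.

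**The covariate may be graded with knowledge of the arm.** This also stands. Under Methods the responsible surgeon opens the envelope once consent is signed, and randomisation comes before the laparotomy. In simulation, a 0.2 SD difference between arms in index grading shifted a null estimate by about 0.05 to 0.09 SD. Entry before icodextrin is instilled does not prevent this, and it is the reason not to let the adjusted result replace the unadjusted one.

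**The power figures do not test an ordinal model.** Correct. They come from linear models, and an ordinal model at 16 v 8 was not evaluated.

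**Conclusion.** The point holds as a modest one about precision. A pre-treatment adhesion record is collected, and the stated analysis of a primary adhesion endpoint does not use it, in a subset of at most about 33 v 16 on the plan's inputs of 65 analysable per arm.

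The size cannot be fixed from the documents. With rho 0.3 to 0.6 and effects of 0.5 to 0.8 SD, all assumed, adjustment adds about 3 to 19 points of power at 33 v 16. If both scores are range-restricted, the gain may be only 1 to 2 points. It may also remove a small measurable part of the imbalance from selection into reoperation.

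Two stronger conclusions are not supported: that the unadjusted tests are invalid, or that adjustment repairs the selected-subset problem.

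**What to change.** 1. Grade index adhesions on the same 0-3 severity score and for extent as at reoperation. Enter the grade before adhesiolysis and, where feasible, before the envelope is opened.
2. Prespecify a comparison at reoperation adjusted for the index value: ANCOVA for extent; for severity an ordinal model, or a linear model on the score if few patients are reoperated.
3. Report the unadjusted test beside the adjusted result.
4. State the limits: the index grade may be arm-aware if the envelope was already open, and adjustment does not remove selection into reoperation.

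**Cost.** One degree of freedom, a few lines of analysis text and a short extra entry at an operation where adhesions are already documented. No extra patients or procedures are needed. Grading before the envelope is opened would mean opening it later than Methods now describes; if that is impractical, the unadjusted result matters all the more. The grading needs to be in place during the inclusion period of about 2 years, since a standard grade is hard to recover afterwards.

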## Methods

The project is a prospective, randomized controlled investigation performed in the Department of Transplant, General and Emergency Surgery of St. Orsola-Malpighi University Hospital [Bologna, Italy]. The study is designed and conducted in compliance with the principles of Good Clinical Practice regulations.

A computer-generated schedule creates the randomized assignments for the subject and control groups and the results are sealed in numbered envelopes. Participation in the study is requested after diagnosing small bowel obstruction caused by adhesions and determining if the patient fulfills the inclusion criteria [subjects who elect to undergo the surgical laparotomy]. Accordingly to the protocol, the patient signs a document indicating his or her consent and the responsible surgeon discloses the envelope.

If after opening the sealed envelope containing the assignments, the patient declines to enter the trial, the case is excluded from the study [all dropped-out patients are reported].

The responsible surgeon will record the patient's name [and number].

Each group has a sample size of 88 patients [176 patients for the whole study].

All randomized patients [Intention to Treat population] are included in the analysis.

Sample size has been calculated to reach a confidence level of 95% with a power of 80%.

A sample size of 88 patients each group [65 analyzable] is calculated supposing that the ASIO patients [first, second, third or fourth operation for ASIO] have a mean risk of 50% to develop a further episode of ASIO and this risk can be decreased by 25% [from 50% to 25%] with the use of Icodextrin 4%

Inclusion criteria are:

Adult patients [> 18 years]

Submitted to laparotomic surgical procedures for ASIO

Clinical and radiological evidence of adhesive small intestine obstruction

ASA I-III patients

Informed consent

Exclusion criteria

Intrabdominal cancer

Peritoneal contamination

IBD

Positive history of radiotherapy

Patients with an intra-operative findings of different pathology will be excluded from the study

Preoperative data include patient demographics, comorbid conditions [genitourinary, cardiac, pulmonary, gastrointestinal, renal, or rheumatologic] and a detailed history of previous occlusions and surgical procedures.

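### Peritoneal contamination is an exclusion that can ordinarily be judged only after the envelope is opened, so applying it allows arm-aware removal of randomised patients

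*Protocol article*

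**What the plan says.** All of the following is in the Methods of the protocol article.

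- **Exclusion.** The exclusion list contains "Peritoneal contamination", with no definition.
- **Assessment.** In the description of the operation, "Peritoneal contamination is evaluated with cultures". No other method is named, and nothing is said about when the result returns or what follows from a positive one.
- **Order of events.** Participation is requested after the diagnosis and after "determining if the patient fulfills the inclusion criteria". Then "the patient signs a document indicating his or her consent and the responsible surgeon discloses the envelope". The second account gives the same order: "written informed consent is obtained from each individual and then they are randomized into the study groups. Laparotomic surgical procedure is carried out".
- **Treatment.** "the second group is treated with Icodextrin 4% before abdomen closure". Controls receive usual treatment, and irrigants during surgery are barred.
- **Admitted patients.** "Subjects are submitted to adhesiolysis with bowel resection if necessary with or without anastomosis". Perioperative data are recorded for all patients, and "Operative wounds are classified as clean, clean contaminated, and contaminated". No exclusion is attached to the last class.
- **Analysis set.** Everyone randomised is to be analysed, as an intention-to-treat population.

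**The concern.** An exclusion criterion protects a randomised comparison only if it is settled before allocation, or by someone who does not know the allocation. Here it is settled after allocation and, on the stated procedure, by a person who has opened the envelope. If a surgeon who knows the arm can decide that a field is contaminated and that the patient therefore does not belong in the trial, the patients left in the two arms need not be comparable. The blinding described in the Design section of the abstract does not help, because it covers third-party assessors of adhesions and not the surgeon at the index operation.

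The criterion is also undefined where it is most likely to be needed. A patient whose bowel is opened at resection, or whose wound is classed as contaminated, is provided for in the account of the operation. The same patient might be excluded under the criteria list. Two surgeons could apply the same text differently.

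**Working it through.** **1. Sequence, with the source of each step**

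| Step | What happens | Status |
|---|---|---|
| 1 | Diagnosis; inclusion criteria checked | Stated |
| 2 | Consent; responsible surgeon opens envelope | Stated |
| 3 | Laparotomy; adhesiolysis, with resection if needed | Stated |
| 4 | Peritoneum seen; contamination can be observed | Follows from step 3 |
| 5 | Culture sample taken | Timing not stated; placed in the account of the operation |
| 6 | Icodextrin given or withheld, before closure | Stated |
| 7 | Culture result available | Not stated; ordinarily after closure |
| 8 | Consequence of a positive culture | Not stated |

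Step 2 falls before surgery on two grounds. The second account puts randomisation ahead of the laparotomy. The Methods also provide for a patient who declines after the envelope is opened, which requires a patient able to answer.

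If contamination is judged by eye, it is judged at step 4. If culture decides, it is judged at step 7. Both come after step 2, so a judgement after randomisation is firm from the text, apart from cases recognised before surgery. A judgement after treatment holds only if culture decides, and rests on the inference at step 7.

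**2. Effect of removal on an arm's event rate**

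Let *R* be the risk of a further obstruction among all patients randomised to an arm, *f* the fraction removed for contamination and *r* the risk among those removed. The risk among those kept is

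(R − f·r) / (1 − f),

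so removal shifts it by f·(R − r) / (1 − f). If *R* is equal in the two arms (no treatment effect) and *f* and *r* are also equal, the shifts cancel. If *f* or *r* differs by arm because the person deciding knows the allocation, they need not cancel, and a difference can appear without any treatment effect. The document gives neither *f* nor *r*, so the shift cannot be evaluated.

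**3. Is this a power problem?**

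Inputs from the Methods: 50% against 25%, 80% power, 95% confidence, 88 per group with 65 analysable. Two-sided testing is assumed.

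- Mean proportion: (0.50 + 0.25)/2 = 0.375.
- n = [1.960·√(2·0.375·0.625) + 0.842·√(0.25 + 0.1875)]² / 0.25² = (1.342 + 0.557)² / 0.0625 ≈ 57.7, so 58 per group.
- With continuity correction: (57.7/4)·[1 + √(1 + 4/(57.7·0.25))]² ≈ 65.4, so 66 rounded up. The stated 65 is reproduced to within rounding.
- Allowance for loss: (88 − 65)/88 = 23/88 = 26.1%; and 65/(1 − 0.26) = 87.8, so 88.

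Power by total loss from all causes, starting from 88 per group:

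| Total loss | Uncorrected | Continuity-corrected |
|---|---|---|
| 10% | 90.9% | 87.8% |
| 20% | 87.3% | 83.2% |
| 26% | 84.6% | 79.8% |
| 30% | 82.6% | 77.2% |
| 40% | 76.4% | 69.5% |

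These losses are a range, not an estimate of contamination. The plan already carries an allowance of about 26%, and power falls slowly around it. What matters is who is removed and by whom, and the sample size does not address that.

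**The case against.** The strongest objection is that nothing in the article says a positive culture removes anyone. Where the protocol does remove patients after randomisation, for bowel leakage and for a different pathology found at operation, it says so in terms. The culture sentence carries no such wording, and the analysis is said to include everyone randomised. On that reading the culture may already be only a recorded descriptor. This stands in part. A reader might infer that treated patients are struck out when the culture returns, but the text supports that only as a possibility. It does not dispose of the point. Contamination remains a listed exclusion, and whether it is judged by eye or by culture, that ordinarily happens after the envelope is opened.

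A second objection is that resection is not peritoneal contamination, and that a wound class describes the wound and not the peritoneum. This stands. A reader might infer that the exclusion contradicts the admitted population. The documents show only an undefined border between an excluded state and admitted ones.

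Third, a condensed article may leave definitions to the full protocol. That is fair for the missing definition alone. It does not cover an exclusion, a sequence and an analysis set that are all stated and do not fit together.

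Two further inferences should not be drawn. Nothing says that those removed would have the most severe obstruction, and nothing presents the exclusion as a safety screen for icodextrin.

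**Conclusion.** The point holds as a weakness in the order of decisions. Applied in the stated sequence, the contamination exclusion is ordinarily decided after randomisation by a surgeon who knows the arm, and removing patients on that basis conflicts with analysing everyone randomised. That the decision comes after treatment is probable only if culture decides it. The border with resected patients and contaminated wounds needs reconciling but is not a direct contradiction.

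The verdict assumes that contamination is seldom recognisable before laparotomy, and that the surgeon who opens the envelope operates or otherwise takes part in the judgement. The number of patients affected cannot be derived, since no resection, contamination or culture-positive rate is given. The consequence is a risk of selective removal of unknown size, not a loss of power. The change should be made, but the point does not by itself invalidate the design.

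**What to change.** 1. Reconcile the exclusion list with the account of the operation. State what counts as peritoneal contamination, who judges it and when. Whether opening the bowel at resection counts is for the sponsor to state.
2. Have the surgeon confirm and record intra-operative eligibility before the envelope is opened. This can be done just before closure, because the arms as described differ only at that moment.
3. Keep culture results and wound class as recorded descriptors. State that a culture result returning later does not remove a randomised patient.
4. Keep every randomised patient in follow-up and in the intention-to-treat analysis.

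**Cost.** No extra patients or data are needed, but this is more than a change of wording. The envelope is opened during the operation instead of before it, so it must be at hand in theatre, and the provision for a patient who declines after it is opened has to be rewritten. Patients found ineligible at laparotomy would have consented without being randomised and should be counted and reported. Some culture-positive patients will stay in the analysis.

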There are no randomized trials on the use of this solution to prevent adhesions after ASIO operation currently present in the medical literature.

The current clinical study evaluates the safety and effectiveness of Icodextrin 4% for decreasing the incidence, extent, and severity of adhesions in patients after abdominal surgery for ASIO.

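### The stated intention-to-treat analysis conflicts with rules that remove randomised patients, including those with bowel leakage, from the results

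*Protocol article*

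**What the plan says.** All the relevant statements are in the Methods of the protocol article.

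- Analysis population: "All randomized patients [Intention to Treat population] are included in the analysis".
- Bowel leakage: "In case of bowel leakage, the patient will no longer be included in the study results".
- Refusal: "If after opening the sealed envelope containing the assignments, the patient declines to enter the trial, the case is excluded from the study". A bracket straight after this adds that all such drop-outs are reported.
- Findings at surgery: "Patients with an intra-operative findings of different pathology will be excluded from the study".
- Order of events: "written informed consent is obtained from each individual and then they are randomized into the study groups. Laparotomic surgical procedure is carried out". Icodextrin is given later, before the abdomen is closed.
- Sample size: "A sample size of 88 patients each group [65 analyzable", for recurrence of 50% against 25%, with 95% confidence and 80% power.

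The Introduction names safety as an aim alongside effectiveness. The Methods collect adverse events from randomisation onwards, register morbidity and mortality, and record other complications during surgery, after it and at each follow-up visit.

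**The concern.** The intention-to-treat statement and the three removal rules give different analysis populations, and nothing in the text says which prevails. The choice would fall to the analysts. Because the primary outcomes are assessed every year, it could be made with data in hand.

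The removals also differ in the harm they can do.

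- **Refusal after opening.** The patient or surgeon may know the arm by then, so losses can be selective.
- **Leakage.** It is always a post-randomisation event here. A leak after closure also follows instillation, so treatment could influence it. Removing such patients then conditions on a possible effect of treatment, and the remaining arms are no longer those that randomisation created.
- **Safety.** If leak patients leave the study results altogether, a serious surgical complication may never be compared between arms, although safety is a stated aim.

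**Working it through.** **1. Can the rules coexist?** Consent and randomisation come first, laparotomy second, icodextrin before closure third. A patient who declines after the envelope is opened, one found to have another pathology, and one who leaks during or after surgery have therefore all been randomised. An analysis of all randomised patients includes them and the removal rules exclude them, so both cannot be followed. This step needs no figures.

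**2. The plan's own sample size.** Inputs from the Methods: p1 = 0.50, p2 = 0.25, power 80%, alpha 0.05 (two-sided assumed). With mean p = 0.375:

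- n = [1.96·√(2·0.375·0.625) + 0.8416·√(0.25 + 0.1875)]² / 0.25² = 57.7
- With continuity correction: (57.7/4)·[1 + √(1 + 4/(57.7·0.25))]² = 65.4

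This reproduces the stated 65. Power = Φ{[0.25·√n − 1.96·√0.46875] / √0.4375} gives 84.6% at 65 per arm and 93.5% at 88 per arm (Fisher's exact test: 80.9% and 91.5%). Analysing all 88 needs no extra patients, provided outcomes are obtained.

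**3. What excluding leak patients could do.** The documents give no leak rate and no recurrence rate after a leak. Assumed: 75% recurrence after a leak. Without a leak, the protocol's own 50% (control) and 25% (icodextrin) are used. For L leaks among 88 patients:

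risk over all patients = [(88 − L)·p + L·0.75] / 88

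| Assumed leaks (control / icodextrin) | Control risk, all 88 | Icodextrin risk, all 88 | Difference, all | Difference, leaks excluded | Shift from exclusion |
|---|---|---|---|---|---|
| 3 / 7 | (85·0.50 + 3·0.75)/88 = 50.9% | (81·0.25 + 7·0.75)/88 = 29.0% | 21.9 | 25 | 3.1 in favour of icodextrin |
| 3 / 3 | 50.9% | (85·0.25 + 3·0.75)/88 = 26.7% | 24.1 | 25 | 0.9 in favour |
| 7 / 3 | (81·0.50 + 7·0.75)/88 = 52.0% | 26.7% | 25.3 | 25 | 0.3 against |

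Counts of 3 and 7 are 3.4% and 8.0% of 88. Over an assumed range of 2% to 15%, about 2 to 13 patients per arm would leave the results. Both the size and the sign of the shift depend on these assumptions.

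**4. Does keeping leak patients cost power?** In the least favourable row (50.9% against 29.0%), the same power formula with 88 per arm gives 84.8%, still above the planned 80%.

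**The case against.** Several points on the other side are sound and limit the claim.

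- **Leaks are not necessarily hidden.** A reader might infer that the plan conceals the main safety event. The documents do not rank leakage in that way, and they collect adverse events from randomisation and record complications throughout. The exclusion may have been meant for efficacy only. What stands is that the text says study results without qualification and does not say that leaks are reported by arm.
- **Timing of the leak is not given.** The neighbouring sentence on a drain suggests a postoperative event, but a leak during surgery, before instillation, is also possible. Such a leak is post-randomisation without being post-treatment. The conflict with intention to treat remains; the argument about a treatment effect applies only to leaks after closure.
- **Refusals are disclosed.** The drop-out bracket is a real safeguard on transparency, though it does not put these patients back into the analysis.
- **Another pathology is a different case.** It is an eligibility failure found before icodextrin is given, and such patients may never have had adhesive obstruction. It should not be treated like a possible outcome of treatment.
- **The 65 of 88.** A reader might infer that these rules remove 23 of 88 patients per arm (26%). The protocol does not tie that shortfall to them. With five years of follow-up, loss to follow-up is an obvious alternative, and enrolling extra patients for missing outcomes does not contradict intention to treat.
- **A larger bias.** Looking only at the icodextrin arm in the 3 / 7 scenario (29.0% against 25%), a reader might infer a 4-point bias. The control arm shifts too, so the risk difference moves by 3.1 points, and other assumed counts give less or reverse the sign.

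**Conclusion.** The contradiction is certain and rests on the text alone: the Methods both include all randomised patients and remove some of them after randomisation. Following the removal rules could bias the recurrence comparison, through refusals made with the allocation known and through leaks that treatment may have influenced. Whether leakage will be reported by arm is unclear; the documents do not support saying that it is suppressed.

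The bias cannot be quantified from the documents. The shifts of 3.1 points and 0.9 points in favour of icodextrin and 0.3 points against it are illustrations. They rest on assumed leak counts, an assumed 75% recurrence after a leak and the protocol's 50% and 25% otherwise. They show that a modest imbalance in leaks can matter, not that it will occur or in which direction.

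**What to change.** - Delete the leak-exclusion sentence as a rule for the primary analysis, and analyse every randomised patient in the allocated arm for recurrence of adhesive obstruction.
- For patients who decline after the envelope is opened, keep outcome data where they consent to this.
- Report bowel leakage by arm as a safety outcome.
- Report all post-randomisation exclusions by arm, with reasons.
- Give the leak-excluded set only as a labelled sensitivity analysis.
- Handle another pathology found at surgery under its own eligibility rule, applied identically in both arms without regard to allocation and reported by arm.

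The cost is more than wording: leak patients and consenting refusers have to be followed for the five years, and keeping them may dilute the effect slightly. No increase in enrolment is needed.
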